Parents who arrive at our website during the study are directed to a brief screening questionnaire that helps identify the most relevant resources for their family and also assesses their eligibility for this study. The automated screener directs only eligible parents to a prerecorded video featuring the study principal investigator ([name]) explaining the purpose of the study and procedures. Interested parents are then directed to the online REDCap (Research Electronic Data Capture; Vanderbilt University) system, a secure, web-based application for survey data collection [22]. Parents provide consent to participate, permission for their son (if he is younger than 18 years of age), and contact information for themselves and their son. Then, they complete their baseline assessment (preintervention) within the REDCap system. Upon completion of the parent assessment, sons are automatically contacted via email or text and invited to participate in an online questionnaire study about “how parents and sons discuss important topics.” Sons are not directly engaged in our intervention and are not informed of the nature of the intervention their parents will receive; these steps decrease GBA resistance to participation (eg, if they want to avoid talking to their parents about sex) and also reduce social desirability bias in their responses (ie, if they understood the intervention goals). Interested sons click a link directing them to the REDCap system, where they provide consent (or assent if younger than 18 years of age) and then complete the baseline assessment. Once parents and sons have completed their initial assessments, the study team receives an electronic alert notifying us that a family is prepared for enrollment in the RCT. At this point, we take a number of steps to ensure that parent-son dyads are legitimate and truly eligible: (1) we first review screener data to identify parents who have completed a screener more than once (eligibility criteria are not advertised, and parents complete the screener naïve to our criteria); parents who have completed the screener multiple times are ineligible unless data from the first assessment indicate that they have multiple children they might have screened for; (2) we next review responses from parent and son assessments to check for consistency (eg, age) and to ensure again that eligibility criteria are met (eg, to ensure that the son has not reported being HIV-positive); and (3) finally, we ask dyads to verify their identities in 1 of 2 ways: either uploading copies of their photo identification or participating together in a brief 5-minute video chat. Families for whom we have concerns about their authenticity or eligibility are required to participate in a video chat to provide clarification about the information they provided. Once verified, parents are considered formally enrolled in the RCT and randomized.

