### Treatment Conditions

Participants assigned to the intervention condition receive both Lead With Love (LWL) and PATHS after randomization. Participants initially assigned to the control condition receive only LWL.

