**Figure 1 figure1:**
[figure not shown]
PATHS conceptual model. GBA: gay and bisexual adolescent; PATHS: Parents and Adolescent Talking About Healthy Sexuality; PrEP: pre-exposure prophylaxis.

To further understand families’ experiences with communicating about sexuality and HIV, we conducted qualitative interviews and focus groups with families. Using these qualitative data as a foundation, together with content from sexual health communication interventions for parents of heterosexual youths, we developed PATHS in collaboration with a volunteer Board of Family Experts, comprised of 4 parents of AMSM and 6 AMSM. Once a working version of the intervention had been developed, it was tested for usability and clarity with 6 parents of AMSM.

PATHS was developed with the goal of changing the following parent behaviors: (1) to increase the overall frequency and quality of parent-adolescent communication about sex and HIV, including communicating about condoms and pre-exposure prophylaxis (PrEP) as means to prevent HIV; (2) to support parents teaching their sons the proper mechanics of condom use; (3) to help parents enable their sons’ access to condoms; and (4) to assist parents in facilitating HIV testing for their sons. These behaviors, in turn, are hypothesized to increase GBA preparedness for sex and ultimately decrease CAVS that is not protected by PrEP.

Parents access PATHS on any web-enabled device with a unique username and password. PATHS is fully automated, self-paced, and designed so parents can access all content in a single session (lasting 30-60 minutes) or in multiple sessions. Content is divided into seven required modules: (1) welcome and overview, (2) importance of communication, (3) HIV information, (4) using and acquiring condoms, (5) PrEP, (6) HIV testing, and (7) a review with a parent “to-do” list. Optional supplemental modules include content on understanding anal intercourse and what to do if a child tests positive for HIV. These topics were deemed optional because they either did not apply to all youths (ie, what to do if a child tests positive) or because parents might not be ready to receive the material (ie, understanding anal intercourse).

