#### One-Month Refreshers

One month after completing the initial intervention assigned, parents are invited to revisit the PATHS web application to complete a “refresher” session designed to reinforce the intervention messaging. The refresher used in this trial was newly developed after the initial pilot RCT of PATHS.

For parents assigned LWL alone, the refresher consists of a series of text pages that summarize the important messages and guidance provided in the original film. For parents assigned PATHS, the refresher first asks parents whether they have been able to successfully engage in each of their selected interactions with their son (ie, the activities they chose to put on their “to-do” list). If a parent indicates that they have not achieved their goal in the previous month, they are presented with a list of possible barriers or reasons why completing the activity was difficult for them. After parents select the barriers they experienced, they are provided with content tailored to each selected barrier designed to help the parents navigate the particular challenge. Once parents review that content, they have the opportunity to reset the goals they did not achieve. Parents also receive reinforcement for any goal they did successfully achieve. Goals that were achieved at the “good” or “better” level are reinforced, and parents are given the opportunity to also set a new goal and achieve the “best” status for a given activity (eg, if they previously just forwarded the condom instruction video to their child, they are asked if they would like to try doing a physical condom demonstration with their child). All new goals that parents set for themselves are recorded on a refreshed to-do list that parents can print or email to themselves.

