#### Analysis Overview

Hypotheses will be tested using multilevel models (MLMs), which are appropriate for nested designs, and allow us to use a single combined model to test treatment effects at 6 months as well as duration of treatment effects from 6 to 12 months. MLMs are also a recommended method for modeling mediation in randomized clinical trials [54]. We will estimate MLMs using gold standard methods for conducting intent-to-treat analyses and for handling missing data. Separate models will be run for each outcome variable, with estimation methods and distributional assumptions adjusted accordingly (eg, hierarchical generalized MLMs for dichotomous outcomes). We will use recommended methods for controlling type I error in randomized clinical trials with more than 1 outcome of interest by adjusting for our false discovery rate in all analyses [55].

Moderators of intervention effects are of potential public health interest (eg, is the intervention similarly effective across age and/or ethnic groups?). Powering this trial to formally test for differences across all potential moderators was prohibitive. However, given the value in demonstrating that intervention effects are robust across groups, we will explore whether treatment effects observed in the full sample are similar to those we observe in subgroups differentiated by the following variables: GBA age, GBA sexual debut status at baseline, GBA race or ethnicity, and degree of parent engagement in the intervention content.

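### Degree of parent engagement arises after randomisation and on different content by arm, so it should not be listed as a moderator subgroup beside baseline variables

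*Protocol article*

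**What the plan says.** In the Analysis Overview the protocol article announces that "we will explore whether treatment effects observed in the full sample are similar to those we observe in subgroups", and names the subgroup variables in one list: "GBA age, GBA sexual debut status at baseline, GBA race or ethnicity, and degree of parent engagement in the intervention content". It gives the reason for keeping this exploratory: "Powering this trial to formally test for differences across all potential moderators was prohibitive". The list does not separate engagement from the other three variables and attaches no caveat to it.

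Other sections fix the timing and the content:

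- Participants: "Once verified, parents are considered formally enrolled in the RCT and randomized". This follows the baseline assessments.
- Treatment Conditions: "Participants assigned to the intervention condition receive both Lead With Love (LWL) and PATHS after randomization", whereas "Participants initially assigned to the control condition receive only LWL".
- Parents and Adolescents Talking About Healthy Sexuality: "Content is divided into seven required modules".
- One-Month Refreshers: "For parents assigned LWL alone, the refresher consists of a series of text pages". The PATHS refresher instead reviews each parent's goals and tailors content to the barriers the parent reports.
- Randomization: control parents are given PATHS only after the 6-month assessment.
- Postintervention Nudges: the article foresees parents who do not complete an activity, and these parents still receive the messages.

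**The concern.** A subgroup comparison keeps the protection of randomisation when the subgroup is fixed before allocation. Age, debut status at baseline, and race or ethnicity meet that condition. Engagement does not, because it can only be observed once a parent has been given the content of the assigned arm.

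The task to be engaged with also differs by arm. A control parent has a 35-minute film and a text refresher. A PATHS parent has the same film, seven required modules (30 to 60 minutes in a single session) and an interactive refresher. Parents called highly engaged may thus be selected differently in the two arms. Alternatively, if engagement is scored on PATHS alone, selected PATHS parents face unselected controls, who have no access to PATHS before month 6.

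What is at stake is the reading of the result. A larger effect among engaged parents could be taken to mean that PATHS works for those who complete it, when part or all of it reflects which parents engage.

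**Working it through.** The article gives no engagement rate, no correlation and no effect size, so there is no figure of its own to reproduce. The check asks how large the bias could be when PATHS does nothing.

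**Inputs from the article:** 1:1 allocation; 350 dyads planned, so 175 per arm; 393 enrolled.

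**Assumptions not in the article:** a standardised outcome scored so that higher is better; true effect 0 for everyone; engagement propensity standard normal, with correlation r to the son's outcome; 60% of PATHS and 85% of control parents above the threshold for high engagement.

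**Step 1, mean propensity in each stratum.** For the top share p of a standard normal with cut-off c, the mean is φ(c)/p. For the remainder it is -φ(c)/(1-p).

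- PATHS: top 60% = 0.644; bottom 40% = -0.966.
- Control: top 85% = 0.274; bottom 15% = -1.555.

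**Step 2, spurious effect = r × difference in mean propensity, with r = 0.3.**

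- Own-arm engagement, high against high: 0.3 × (0.644 - 0.274) = +0.11 SD.
- Own-arm engagement, low against low: 0.3 × (-0.966 + 1.555) = +0.18 SD.
- High PATHS against all controls: 0.3 × (0.644 - 0) = +0.19 SD.
- Low PATHS against all controls: 0.3 × (-0.966 - 0) = -0.29 SD.

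**Step 3, simulation** (6,000 runs per row, N = 350, two-sided 5% tests, true effect 0). The last column is how often the high and low strata appear to differ.

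| Comparison | r | Bias high (SD) | Bias low (SD) | False positive, high | False positive, low | False difference |
|---|---|---|---|---|---|---|
| Own arm, 60% v 85% | 0 | 0.00 | 0.00 | 5% | 6% | 6% |
| Own arm, 60% v 85% | 0.1 | +0.04 | +0.06 | 6% | 6% | 5% |
| Own arm, 60% v 85% | 0.2 | +0.07 | +0.12 | 9% | 9% | 6% |
| Own arm, 60% v 85% | 0.3 | +0.11 | +0.18 | 14.5% | 13% | 6% |
| Own arm, 70% v 70% | 0.3 in both | 0.00 | 0.00 | 5% | 6% | 5.5% |
| Own arm, 70% v 70% | 0.3 PATHS, 0.1 control | +0.10 | -0.23 | 12% | 23% | 30% |
| PATHS strata v all controls | 0.1 | +0.07 | -0.10 | 9% | 10.5% | 19% |
| PATHS strata v all controls | 0.2 | +0.13 | -0.19 | 19% | 28% | 55% |
| PATHS strata v all controls | 0.3 | +0.19 | -0.29 | 36% | 54% | 89% |

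With the 393 enrolled and r = 0.3 the biases are essentially the same (+0.11 and +0.18; +0.19 and -0.29).

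**Reading the table.** With own-arm strata and equal correlations, both strata are biased in favour of PATHS, slightly more in the low stratum, and the difference between strata is flagged at close to the nominal rate. A false dose-response appears when PATHS strata are set against all controls, or when engagement relates to outcome more strongly in the PATHS arm.

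**The case against.** The strongest objection is that little hangs on this. The article calls the subgroup work exploratory and unpowered, the main analysis is intent-to-treat, and false discovery rate adjustment is promised for all analyses. That limits the impact, and it stands. The adjustment does not help here, however, because it addresses multiplicity and not selection.

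Second, the article does not say how engagement is scored, or whether it is scored in controls. The film is common to both arms, and the analysis plan, which is not shown, may define the measure. This also stands as far as it goes: engagement with the film alone would cover common content. It would still be a post-randomisation variable, and the choice to list it among moderators is made in the article itself.

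Third, the rates and correlation above are mine. Under Ethical Considerations, engaging in the intervention is one of three requirements for the first parent payment, with no distinction by arm, which may raise and equalise engagement. If share and correlation are equal, the bias is about zero.

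A reader might go further and infer that this subgroup is bound to show a spurious effect, or a dose-response even if PATHS were inert. The documents do not support that. Bias depends on conditions the article does not state, and under the own-arm 60% against 85% scenario the spurious effect is larger among less engaged parents. Nor does the article say that similarity will be judged without interaction tests or confidence intervals; that detail may properly sit in the analysis plan.

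**Conclusion.** The point holds as a matter of design: a variable that arises after randomisation, and refers to different content by arm, is listed as a moderator beside three baseline variables, so treatment comparisons within its levels are not randomised. They can be biased; it is not certain that they will be. Across the assumed correlations of 0 to 0.3 the spurious effect runs from zero to roughly 0.3 SD in absolute size, and its direction depends on how engagement is defined and which controls are used. All of these sizes rest on assumed engagement rates and correlations. The primary intent-to-treat comparison and the three baseline moderators are untouched.

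**What to change.** Remove degree of parent engagement from the moderator list and keep the three baseline variables. Report engagement separately, in one of two ways:

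- an exploratory dose-response analysis, labelled as non-randomised; or
- a complier (principal-stratum) analysis at 6 months with randomisation as the instrument. Control parents are not given PATHS before then, so non-compliance with PATHS is one-sided.

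Either needs a stated definition of engagement. The complier analysis also needs its assumptions written down. In particular, the exclusion restriction is not automatic: the messages promoting PATHS behaviours also go to parents who do not complete activities, so assignment may act on non-compliers. A threshold as low as opening any one module would not answer a question about degree of engagement, and would return nearly the intent-to-treat effect if almost every parent met it.

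The cost is a change of wording and one extra exploratory analysis, with no new outcome data. The research team is unblinded and results are projected for the first quarter of 2027, so the definition should be fixed before outcomes are analysed.

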## Results

The study was funded in March 2022, and we completed enrollment of 393 parent-GBA dyads in September 2025. We project that all participants will have completed study activities by November 2026, with data analysis and results of the trial forthcoming in the first quarter of 2027.

## Discussion

### Potential Implications of Findings

GBA are the group of teens at highest risk for HIV infection in the United States, but evidence-based interventions to reduce that risk are extremely limited. If we demonstrate that PATHS reduces sexual risk behaviors or improves adolescent preparedness for sex, it will provide a new option for addressing an ongoing public health challenge. Additionally, to our knowledge, PATHS will be the first intervention for GBA that addresses a system of influence beyond the individual level. This is critical because not all adolescents are interested in engaging directly in HIV prevention interventions themselves. Having the option of reaching teens via their parents provides a valuable alternative for the field, ensuring that a greater number of adolescents have support for their sexual health.

This trial also aims to expand the field’s approach to assessing sexual health outcomes for adolescents. Clearly, the goal in any sexual health intervention is to reduce the incidence of poor health outcomes (STIs, HIV, and unplanned pregnancy). In the absence of extremely large samples and long follow-up periods, those outcomes will be difficult to detect among adolescents in any intervention trial. Thus, the widely accepted compromise has been to measure self-reported behaviors that are a clear part of the causal chain to incident disease or pregnancy (eg, condomless sex). However, those behavioral outcomes also carry limitations: self-reports are imperfect, and even when they are assessed reliably, those behaviors also must be common enough to create an opportunity for intervention effects to be observed. Often, the solution to the challenge of low behavioral frequency is for trials to recruit only GBA with histories of risk behavior or significant sexual experience. However, sexual health interventions might have different effects for youths who have already established patterns of sexual behavior, relative to youths who are less experienced. If trials preselect youths already engaging in risk behaviors, we will know less about intervention effects on GBA who have yet to initiate sex or sexual risk. Our approach in this trial is to test effects not only on self-reported behaviors but also on outcomes that can be reliably assessed in any adolescent (eg, photo-verified possession of condoms and demonstrated skill using a condom), regardless of their level of prior sexual experience.

Finally, this trial aims to advance our understanding of how parent-focused interventions achieve their effects. Parent-focused intervention trials rarely publish results from mediation analyses that specify how parent behaviors changed as a result of the intervention and how those parent changes related to improvements in adolescent sexual health. By examining these processes, this trial will help future interventions focus their efforts on the parent behaviors most likely to protect adolescents.

### Limitations

This intervention trial uses “sexual preparedness” as a primary outcome. While this approach has the strengths outlined earlier, we must also recognize its limitations. For example, we cannot know for certain whether youths who are in possession of condoms, and who demonstrate correct condom application skills, will necessarily use them consistently in their future sexual encounters. Longitudinal research does show that youths who use condoms in their first sexual encounter are more likely to use condoms up to 7 years later and are less likely to contract STIs during that time [56]. However, future longitudinal research should identify other early indicators that are reliably associated with subsequent disease or pregnancy in order to expand the list of potential proximal intervention outcomes that reliably predict sexual health outcomes throughout adolescence.

Another limitation of this trial is that not all parents have the time, interest, or ability to participate in a parent-focused intervention. Moreover, not all parents of GBA are open with their parents about their sexual orientation. Thus, this intervention, like any intervention, will not reach every GBA. Our prior research demonstrates that GBA who have disclosed their sexual orientations to their parents are actually more likely to engage in sexual risk behaviors than their peers who have not yet disclosed [17,57], so we are confident that parent-focused intervention can reach youths at risk for HIV and STI infection. Nevertheless, parent-focused approaches will be most effective at reducing population-level HIV risk if they are accompanied by a suite of other intervention options, including those that are offered directly to adolescents themselves, as well as those that seek to create change at broader sociostructural levels (eg, by changing schools, clinical practice, or communities).

Finally, while our cross-over design allows us to test intervention effects in the first 6 months using a traditional “pure” control group that has received no intervention relevant to sexual health, this design comes with compromises in testing the duration of intervention effects at 12 months. Specifically, the estimates of longer-term effects must be made by comparing data from intervention families from 6 to 12 months after the intervention to model-based estimates we make about where control families would be from 6 to 12 months if they had not crossed over and received intervention. Those estimates are based on the data the control families provide from baseline to 6 months. The advantages of this approach are that all families enrolled in the study end up with timely access to an intervention with preliminary evidence of efficacy. It also provides a second opportunity to examine intervention effects in the control group by making a within-subject comparison of data from 6 months prior to intervention to 6 months after the intervention. We characterize the test of duration of intervention effects as a secondary aim, given that the tests of those effects rely on model-based estimates of a control effect, rather than a true control.

